##### (vi) Plantar pressure measurement

Plantar pressures will be recorded during level barefoot walking using the MatScan^® ^system (Tekscan^®^, Boston, MA, USA). The two-step gait initiation protocol will be used to obtain foot pressure data, as it requires fewer trials than the mid-gait protocol and has similar re-test reliability [32]. Three trials will be recorded, which has been found to be sufficient to ensure adequate reliability of pressure data [32,33]. Following data collection, the Research Foot^® ^software (version 5.24) will be used to construct individual "masks" to determine maximum force (kg) and peak pressure (kg/cm^2^) under seven regions of the foot: hallux, lesser toes, 1^st ^MPJ, 2^nd ^MPJ, 3^rd ^to 5^th ^MPJs, midfoot and heel (Figure 4a). For each region, the median of the three trials will be used for analysis. Typical plantar pressure recordings from a participant are shown in Figure 4b.

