### Sample size

The sample size for the study has been pre-specified using an *a priori *power analysis using the primary outcome measure of the pain domain of the FHSQ [42]. One hundred and forty two participants (i.e. 71 per group) will provide power of 90% to detect a minimally important difference in the pain domain of the FHSQ (i.e. 14 points on the FHSQ questionnaire) with the significance level set at p < 0.05. A difference of 14 points was determined to be a clinically significant difference worth detecting [43] and a standard deviation of 25 was derived from a previous report [44]. This calculation included a 5% drop-out rate [13]. However, we will aim to recruit 150 participants (~75 participants per intervention group). Further, we have conservatively ignored the extra precision provided by covariate analysis when estimating the sample size.

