### Statistical analysis

Statistical analysis will be undertaken using SPSS version 14.0 (SPSS Corp, Chicago, Ill, USA) and STATA 8 (Stata Corp, College Station, Tex., USA) statistical software. All analyses will be conducted on an intention-to-treat principle using all randomised participants [45-47]. Missing data will be replaced with the last score carried forward [48]. Standard tests for normal distribution will be used and transformation carried out if required.

Demographic characteristics (gender, age, weight, height, body mass index) will be determined for the baseline visit for each treatment group. Summary statistics will be calculated for duration of symptoms, side affected (left, right, bilateral), grade of OA at the first MPJ [19] as well as all primary and secondary outcome measurements for each treatment group.

Analyses will be conducted on 1, 3 and 6 month outcome measures. The continuously-scored outcome measures at 1, 3 and 6 months will be compared using analysis of covariance with baseline scores and intervention group entered as independent variables [49,50]. The exception to this will be the plantar pressure measurements which will be analysed at baseline, 1, 3 and 6 months using two-way repeated measures analysis of variance statistics. Post-hoc comparisons will be performed using Bonferroni-adjusted t-tests. Nominal and ordinal scaled data will be compared at 1, 3 and 6 months using Mann-Whitney U-tests and chi-square analyses (or Fisher's exact test where appropriate) respectively. Effect sizes will be determined using Cohen's *d *(continuous scaled data) or odds ratios (nominal scaled data and ordinal scaled data) as appropriate.

The outcome measurements obtained at 7 or 9 months for participants that receive a second and final intra-articular injection (of Synvisc^® ^or sterile saline according to the treatment group they are in) on days 30 or 90 respectively, will also be analysed as described above. These analyses will be classified as secondary outcomes.

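### Plantar pressure is exempted, without a stated reason, from the baseline-adjusted ANCOVA used for the other continuous outcomes; restoring it is a free gain in precision and clarity on a secondary outcome

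*Protocol article*

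**What the plan says.** In the protocol article, Statistical analysis, continuous outcomes at 1, 3 and 6 months "will be compared using analysis of covariance with baseline scores and intervention group entered as independent variables". The next sentence makes one exception, the "plantar pressure measurements which will be analysed at baseline, 1, 3 and 6 months using two-way repeated measures analysis of variance statistics". No reason is given. It is followed by: "Post-hoc comparisons will be performed using Bonferroni-adjusted t-tests". The text does not say whether these t-tests compare groups or time points, whether they use raw values or changes from baseline, or which comparisons form the Bonferroni family.

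The exempted outcome is secondary. Under Plantar pressure measurement, the masks are used to "determine maximum force (kg) and peak pressure (kg/cm^2^) under seven regions of the foot", so there are 7 × 2 = 14 variables. The Sample size section recognises what a baseline covariate brings: "we have conservatively ignored the extra precision provided by covariate analysis when estimating the sample size".

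**The concern.** Baseline is collected for plantar pressure as for every other outcome, but here it enters the model as a response and not as a covariate. This affects each output of the planned analysis differently.

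- **Group main effect.** It averages over four visits, one of them before the injection, when no treatment effect can exist.
- **Group-by-time interaction.** It uses baseline through within-person change, but it is an omnibus test on 3 degrees of freedom. It does not say at which visit the groups differ, or by how much.
- **Post-hoc t-tests.** The answer at each visit has to come from these. As written they carry no baseline covariate, so between-group versions are less precise than the ANCOVA used elsewhere in the plan. Within-group versions would not be a randomised comparison at all.

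At stake are the precision and readability of the plantar pressure results.

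**Working it through.** **The plan's own figure.** The stated sample size reproduces: 2 × (1.960 + 1.282)² × (25/14)² = 67.0 per group, and 67.0/0.95 = 70.5, so 71 per group and 142 in total. It concerns FHSQ pain and has no bearing on plantar pressure. It only supplies the group size used below.

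**Inputs.** From the documents: 71 per group, visits at baseline and 1, 3 and 6 months, and "with the significance level set at p < 0.05" (taken as two-sided). Assumed, because the documents give nothing for plantar pressure: a constant effect d = 0.4 SD at all three follow-ups, equal variances, and the same correlation rho between any two visits, with rho from 0.3 to 0.8.

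**1. Dilution of the main effect.** The average effect over four visits is (0 + d + d + d)/4 = 0.75d. This needs no assumption about rho.

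**2. Relative variance at one visit.** With a raw-value t-test set to 1, ANCOVA has variance 1 − rho² and a change-score t-test has 2(1 − rho). ANCOVA relative to the change score is therefore (1 − rho²)/[2(1 − rho)] = (1 + rho)/2.

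| rho | ANCOVA / raw t-test | ANCOVA / change score |
|---|---|---|
| 0.3 | 0.91 | 0.65 |
| 0.5 | 0.75 | 0.75 |
| 0.7 | 0.51 | 0.85 |
| 0.8 | 0.36 | 0.90 |

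**3. Power at one visit, same correction for each test.** Alpha is 0.05/3 = 0.0167. The noncentrality of the raw t-test is 0.4 × √(71/2) = 2.38. It is divided by √(1 − rho²) for ANCOVA, giving 2.50, 2.75, 3.34 and 3.97, and by √[2(1 − rho)] for the change score, giving 2.01, 2.38, 3.08 and 3.77. Power from the noncentral t distribution:

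| rho | Raw t-test | Change-score t-test | ANCOVA |
|---|---|---|---|
| 0.3 | 0.49 | 0.34 | 0.53 |
| 0.5 | 0.49 | 0.49 | 0.63 |
| 0.7 | 0.49 | 0.74 | 0.82 |
| 0.8 | 0.49 | 0.91 | 0.94 |

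Simulation of the same setting at rho 0.7 gives 0.72 for the change score and 0.80 for ANCOVA, within about 0.02 of these values.

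**4. The two ANOVA tests, alpha 0.05.** For the main effect, the effect is 0.75 × 0.4 = 0.30 and the variance of a four-visit mean is (1 + 3rho)/4. For the interaction, the noncentrality is (71/2) × 0.75 × 0.4²/(1 − rho) = 4.26/(1 − rho), on 3 and 420 degrees of freedom. The last column is ANCOVA at one visit, also at alpha 0.05.

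| rho | Group main effect | Interaction | ANCOVA, one visit |
|---|---|---|---|
| 0.3 | 0.73 | 0.52 | 0.70 |
| 0.5 | 0.61 | 0.68 | 0.78 |
| 0.7 | 0.52 | 0.90 | 0.91 |
| 0.8 | 0.49 | 0.98 | 0.98 |

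The main effect loses power as rho rises, which is where a baseline covariate would help most. The interaction catches up with ANCOVA by rho 0.7.

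**The case against.** The strongest defence is that the effect in a pre-post repeated-measures ANOVA is normally read from the group-by-time interaction. That test uses each person's baseline, and it matches single-visit ANCOVA at rho 0.7 and above. A reader might infer that the plan throws the baseline away; for the model as a whole that is not so. The protocol also never names the main effect as its test. This part of the defence stands. The interaction still gives no between-group difference at a named visit.

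A reader might also take the post-hoc t-tests to be uncorrected. They are not: the protocol states a Bonferroni adjustment, and what is absent is a baseline covariate. Nor does the text say that they use raw values or that baseline belongs to the family. Setting a raw-value test corrected for four comparisons (0.44 at any rho) against an uncorrected ANCOVA (0.91 at rho 0.7) would therefore exaggerate the loss. The like-for-like comparison is the table under one correction, and if the tests are on change scores the gap at high rho is small.

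The protocol plans Cohen's d for continuous data, so some effect size would be reported. It does not say whether this is baseline-adjusted or at which visits it applies.

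Finally, the outcome is secondary, does not drive the sample size and is missing from the outcome list in the Discussion. That limits the weight of the point. It does not supply a reason for the exception.

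**Conclusion.** The point holds as a free improvement of minor weight. Plantar pressure is the one continuous outcome taken out of the baseline-adjusted analysis. No reason is given, and the same article credits covariate analysis with extra precision.

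The dilution of the main effect to three quarters is arithmetic for a constant effect. ANCOVA is more precise than a raw-value t-test at any non-zero rho, and more precise than a change-score test at any rho below 1. The size of the gain rests on the assumed rho and the assumed 0.4 SD effect. Against a raw-value test it runs from slight (0.49 to 0.53 at rho 0.3) to large (0.49 to 0.94 at rho 0.8). Against a change-score test it runs the other way, from 0.34 to 0.53 at rho 0.3 down to 0.91 to 0.94 at rho 0.8.

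A reader might infer that the exception biases the plantar pressure results. The documents do not support that: with randomised groups, the cost is in efficiency and interpretability only.

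**What to change.** Delete the sentence that makes the exception. Analyse maximum force and peak pressure in each region by the ANCOVA already specified, with baseline score and group, at 1, 3 and 6 months. A repeated-measures model of the three follow-up values with baseline as covariate would also serve. Report adjusted between-group differences with confidence intervals at each visit.

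Keep the Bonferroni adjustment for these comparisons, and state whether its family is the three visits only or also the 14 variables. Dropping that sentence together with the exception would leave 14 × 3 = 42 comparisons at 0.05, or 42 × 0.05 = 2.1 expected false positives if there were no effect anywhere.

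The change needs no new data, visits or participants, only an edit to two sentences before the data are analysed.

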#### Baseline assessments and outcome measures

Participants who are eligible for the study will be invited to attend a baseline assessment. During the baseline assessment, participants will undergo primary and secondary outcome measurements prior to receiving their injection. The outcome measurements have been developed in accordance of the recommendations of the OARSI Clinical Trials Task Force guidelines [18].

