#### Primary outcome measures

Outcome measurements (primary and secondary) will occur at four time-points at baseline, 1, 3 and 6 months post-treatment (after the intra-articular injection of Synvisc^® ^or placebo). The assessor performing the measurements will be blinded as to which treatment group participants have been allocated to. Participants who receive a second treatment at day 30 or 90 will be followed for a further 30 days or 90 days respectively and undergo outcome measurements at 7 or 9 months respectively.

The primary outcome measures will be the *Pain *and *Function *subscales of the Foot Health Status Questionnaire (FHSQ) [24]. The FHSQ includes 13 questions that assess four domains of foot health, *Foot pain, Foot function, Footwear *and *General foot health*. The FHSQ has been subjected to an extensive validation (content, criterion and construct validity) process. It has a high test-retest reliability (intraclass correlation coefficients ranging from 0.74 to 0.92) and a high degree of internal consistency (Cronbach's α ranging from 0.85 to 0.88) [24]. Rigorous reviews have rated it as one of the highest quality foot health status measures currently available [25-27].

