##### (ii) Severity and duration of stiffness at the first metatarsophalangeal joint

The severity of stiffness at the first MPJ during walking over the past week will be assessed using a 100 mm visual analogue scale. The left side of the scale (0 mm) will be labelled "not stiff at all" and the right side of the scale (100 mm) will be labelled "most stiff possible". The average duration of stiffness at the first MPJ over the past week will be assessed using a four category scale response. The responses are: "none", "1–15 minutes", "16–30 minutes" and "greater than 30 minutes" [29].

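### Stiffness duration is recorded before injection, but the tests fixed for ordinal outcomes cannot use that baseline, at a modest cost in power on this one secondary outcome

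*Protocol article*

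**What the plan says.** Secondary outcome (ii) has two parts, severity and duration of stiffness. Severity is a 100 mm visual analogue scale. For the other part, "The average duration of stiffness at the first MPJ over the past week will be assessed using a four category scale response"; the categories are none, 1–15, 16–30 and more than 30 minutes.

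The schedule under Primary outcome measures covers both classes of outcome: "Outcome measurements (primary and secondary) will occur at four time-points at baseline, 1, 3 and 6 months post-treatment". Baseline assessments and outcome measures confirms that at baseline "participants will undergo primary and secondary outcome measurements prior to receiving their injection". Stiffness duration therefore has a pre-treatment value on the same scale as its follow-up values.

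The Statistical analysis section assigns methods by type of scale:

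- Continuous: "The continuously-scored outcome measures at 1, 3 and 6 months will be compared using analysis of covariance with baseline scores and intervention group" as independent variables, with plantar pressure as the named exception.
- Nominal and ordinal: "Nominal and ordinal scaled data will be compared at 1, 3 and 6 months using Mann-Whitney U-tests and chi-square analyses". The same sentence allows the Fisher test as a substitute.
- Effect size for the second class: "odds ratios (nominal scaled data and ordinal scaled data) as appropriate". No model or covariate is given for this odds ratio.

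**The concern.** The tests named for ordinal data compare the follow-up categories of the two arms and ignore where each participant began. For satisfaction with treatment and self-reported symptom change that is right, since neither has a value before injection. Stiffness duration does have one.

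If a participant's baseline category predicts the later category, some of the follow-up variation could be explained and removed from the comparison. The Sample size section itself notes that covariate analysis adds precision. At stake is a somewhat higher chance of missing a real effect on stiffness duration. The two FHSQ primary outcomes already have baseline adjustment, and neither they nor the sample size are affected.

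This is a method the article states, not a detail left to a fuller document.

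**Working it through.** **1. The plan's own figure.** Inputs from the Sample size section: difference 14, SD 25, significance level 0.05 (taken as two-sided), power 90%, drop-out 5%.

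n per arm = 2 × (1.960 + 1.282)² × 25² / 14² ≈ 67.01, rounded up to 68. The t-test version gives 67.99. Allowing for drop-out: 67.99 × 1.05 = 71.4, or 67.99 / 0.95 = 71.6. The stated 71 per group reproduces and is not in dispute. It is used below as the number per arm.

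**2. What the protocol does not give for stiffness duration.** There is no effect size, no category shares and no correlation between baseline and follow-up. All three are assumptions here. The value 14/25 = 0.56 SD is the target for FHSQ pain and serves only as one point in a range.

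**3. Method.** Baseline and follow-up are drawn from a bivariate normal distribution with correlation rho. Each is cut into four categories, and the treated arm's follow-up is shifted by d SD. Power is the share of simulated trials with two-sided p < 0.05.

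*Run A.* 3,000 trials per setting; baseline cuts at 10/50/75%, control-arm follow-up cuts at 15/50/80%. Mann-Whitney against a baseline-adjusted (Quade) rank test:

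| d | rho | Mann-Whitney | Adjusted | Gain (points) |
|---|---|---|---|---|
| 0.45 | 0.3 | 0.700 | 0.735 | 3.5 |
| 0.45 | 0.5 | 0.704 | 0.783 | 7.9 |
| 0.45 | 0.7 | 0.696 | 0.877 | 18.1 |
| 0.56 | 0.3 | 0.868 | 0.887 | 1.9 |
| 0.56 | 0.5 | 0.868 | 0.930 | 6.2 |
| 0.56 | 0.7 | 0.877 | 0.973 | 9.6 |

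With d = 0, rejection rates were 0.040 to 0.050 for both methods. A proportional-odds model with baseline, run at d = 0.45 over 400 trials, gave 0.78 at rho 0.5 and 0.86 at rho 0.7, close to the adjusted rank test.

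*Run B.* A separate simulation at d = 0.5 with category shares 15/35/30/20% and 400 trials per setting (Monte Carlo standard error about 0.02). The adjusted method is proportional-odds regression with baseline category:

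| rho | Mann-Whitney | Chi-square | Adjusted | Gain over Mann-Whitney (points) |
|---|---|---|---|---|
| 0 | 0.79 | 0.63 | 0.80 | about 1 |
| 0.3 | 0.79 | 0.65 | 0.81 | about 2 |
| 0.5 | 0.76 | 0.60 | 0.85 | about 9 |
| 0.7 | 0.73 | 0.59 | 0.94 | about 21 |

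In run B the adjusted rank test gave 0.79, 0.80, 0.84 and 0.94.

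**4. Reading the tables.** The gain rises with rho and is essentially nil at rho 0. At rho 0.3 it lies within simulation error in run B. True Mann-Whitney power cannot depend on rho, so the drift from 0.79 to 0.73 in run B is noise, and the 21 points are probably somewhat high. Against the mean of the four unrounded Mann-Whitney values, (0.7875 + 0.79 + 0.7625 + 0.7275) / 4 = 0.767, the gain at rho 0.7 is 0.9425 − 0.767 = 0.176, or about 18 points.

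**5. Why the gain has this shape.** In run B's setting, the share of rank variance left after using baseline, 1 − r², is 0.93, 0.81 and 0.61 at rho 0.3, 0.5 and 0.7. Unexplained variance therefore falls by about 7%, 19% and 39%.

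**The case against.** The strongest reply is that nothing here is wrong. A two-sample rank test is a conventional and valid analysis of an ordinal secondary outcome in a randomised trial, and the simulated type I error is close to 5% with or without adjustment. That stands: this is a case for a better test, not against an invalid one.

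Four stronger readings are tempting and are not supported.

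- *Chance baseline imbalance biases the comparison.* It does not. Such imbalance is already allowed for in the test's error rate. Baseline values are also summarised by arm, so any imbalance would be visible.
- *The plan contradicts itself by adjusting stiffness severity but not stiffness duration.* It applies one rule by type of scale, and the two parts of this outcome have different scales.
- *The plan's own effect of 0.56 SD applies here.* That is the FHSQ pain target. Nothing comparable is stated for stiffness duration.
- *The loss is much larger because chi-square may be the intended test.* Read literally, the word order in the sentence sends ordinal data to chi-square. The gap to the adjusted model in run B would then be about 16 to 35 points over rho 0.3 to 0.7. But a gap of about 17 points (0.80 − 0.63) exists even at rho 0, where baseline carries no information. That part comes from ignoring category order, which is a separate matter. Neither test uses baseline, so the present point holds on either reading.

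It is also fair that adjustment changes the estimand. Odds ratios are non-collapsible, so an odds ratio conditional on baseline is not simply a more precise version of the unadjusted one. What has been shown is a gain in power.

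**Conclusion.** The point holds as a minor improvement. A baseline on the same scale is collected before injection, and the stated tests for ordinal data cannot use it. The result is lower power than the data allow for stiffness duration, with no bias.

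The size cannot be fixed from the protocol. Under the assumptions shown (71 per arm, four categories, shift of 0.45 to 0.56 SD), the loss against Mann-Whitney is about 2 to 4 points at rho 0.3, 6 to 9 at rho 0.5 and 10 to 21 at rho 0.7, the upper end being partly simulation noise. If rho is near 0.3 or lower, the choice hardly matters. The trial's main conclusion does not depend on it.

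**What to change.** Add one sentence to Statistical analysis: stiffness duration at 1, 3 and 6 months will be compared by proportional-odds regression with intervention group and baseline stiffness-duration category as independent variables. The odds ratio should be reported and labelled as baseline-adjusted (conditional). Name a baseline-adjusted rank test as the alternative if proportional odds is doubtful or categories are sparse. Keep the two-sample rank test for satisfaction and symptom change.

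This also supplies a model for the odds ratio that the plan already names for ordinal data. Fixing it before unblinding avoids a later choice between adjusted and unadjusted results.

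The cost is analysis wording only, with no new data, visits or participants. The downside is a proportional-odds assumption and possible pooling of sparse categories.

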##### (vi) Global satisfaction with the treatment

Global satisfaction with the treatment will be assessed using a 5-point Likert scale, as well as a dichotomous (yes/no) scale. The five point-Likert scale will ask "How satisfied are you with the treatment you received for your big-toe joint pain?", and will have the following five responses: "Dissatisfied", "Only moderately satisfied", "Fairly satisfied", "Clearly satisfied" and "Very satisfied". The dichotomous scale of satisfaction will be answered as "Yes"' or "No" in response to the question: "Would you recommend the treatment that you received to someone else with big-toe joint pain".

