##### (viii) Self-reported magnitude of symptom change

Self-reported magnitude of symptom change will be measured using a 15-point Likert scale. The scale will ask participants "how much have your symptoms in your big-toe joint have changed from the beginning of the study to now?". The fifteen responses will range from "A very great deal better" to "A very great deal worse".

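### The tests for nominal and ordinal data are named in the wrong order, so three ordinal secondary outcomes would get a test that ignores category order and loses power

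*Protocol article*

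**What the plan says.** The Statistical analysis section sets one rule for all outcomes that are not continuously scored. It names the data types first and then the tests: "Nominal and ordinal scaled data will be compared at 1, 3 and 6 months using Mann-Whitney U-tests and chi-square analyses". The part of the sentence that names the tests reads in full "using Mann-Whitney U-tests and chi-square analyses (or Fisher's exact test where appropriate) respectively". A later sentence in the same paragraph sets the effect measure for both types: "odds ratios (nominal scaled data and ordinal scaled data) as appropriate".

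The outcomes with ordered categories are listed under Secondary outcome measures:

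- duration of stiffness, "assessed using a four category scale response", running from none to more than 30 minutes;
- satisfaction: "Global satisfaction with the treatment will be assessed using a 5-point Likert scale", with a separate yes/no item on recommending the treatment;
- symptom change, "measured using a 15-point Likert scale", running from much better to much worse.

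The primary outcomes, FHSQ pain and function, fall under a different rule: analysis of covariance with the baseline score.

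**The concern.** The closing word of the sentence fixes the pairing. Nominal data, named first, take the Mann-Whitney test, and ordinal data, named second, take chi-square or Fisher's exact test. No other section corrects this.

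Mann-Whitney ranks the observations, so it has no meaning for unordered categories. Chi-square and Fisher's exact test, as named, treat categories as unordered labels. Applied to an ordered scale, they ask whether the two distributions differ in any way, not whether one arm does better. The evidence of a consistent shift is spread over k − 1 degrees of freedom, where k is the number of categories, instead of being concentrated in one. A real benefit on patient-rated change could therefore be missed. An analyst who noticed the problem late would have to follow a wrong rule or depart from the published one, and a departure after unblinding invites the suspicion that the test was chosen by its result.

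**Working it through.** **1. Which outcomes fall under the rule.** Stiffness duration has k = 4 (3 df), satisfaction k = 5 (4 df) and symptom change k = 15 (14 df). The 15-point scale does not fit the continuous rule as written: that rule needs a baseline score, and a rating of change since the start of the study has none. The same holds for satisfaction.

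**2. The plan's own figure.** The Sample size section gives 14 points, SD 25, 90% power and p < 0.05. Two-sided, n per arm = 2 × (1.960 + 1.282)² × 25² / 14² ≈ 67, or 68 with the t correction. Allowing for 5% drop-out gives 68 / 0.95 = 71.6, or 68 × 1.05 = 71.4, against the stated 71. This agrees to within rounding. The standardised difference is 14 / 25 = 0.56. No power is stated for any ordinal outcome.

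**3. Simulation at 71 per arm, two-sided 5% level.** Assumptions: placebo probability 1/k in each category; active-arm cumulative probability Φ(Φ⁻¹(j/k) − 0.56) at category j.

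- Chi-square: the sum of (observed − expected)² / expected over the 2 × k table, on k − 1 df.
- Mann-Whitney: z = (W − n(N+1)/2) / √{(n²/12)[(N+1) − Σ(t³ − t)/(N(N−1))]}, where W is the rank sum in one arm, n the number per arm, N = 2n, and t the pooled category counts.

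| Outcome | Chi-square | Mann-Whitney | Loss in points | Relative loss |
|---|---|---|---|---|
| 4 levels | 73% | 85% | 12 | 12/85 = 14% |
| 5 levels | 70% | 87% | 17 | 17/87 = 20% |
| 15 levels | 44% | 90% | 46 | 46/90 = 51% |

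Repeat runs agree to within about 2 percentage points. Type I error is near 5% for both tests. With 15 levels the expected count is at best 71/15 = 4.7 per cell, so the table may be sent to Fisher's exact test, which ignores order as well.

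**4. Range over the assumed shift.** For 15 levels, power is 20% vs 63% at 0.4 SD and 82% vs over 99% at 0.8 SD. For 4 and 5 levels at 0.8 SD it is 95–96% vs 99%.

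**5. Cross-check without the 0.56.** Suppose an ordered 1-df test has a given power. Its noncentrality is λ = (1.960 + z_power)², which is 7.85 at 80% and 10.51 at 90%. The same λ on more degrees of freedom gives:

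| Ordered test | 3 df | 4 df | 14 df |
|---|---|---|---|
| 80% | 64.5% | 59.5% | 36.7% |
| 90% | 78.4% | 74.0% | 49.8% |

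**6. Cross-check under another model.** With a proportional-odds shift, 75 per arm and several category shapes, chi-square vs Mann-Whitney power is:

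| Assumed odds ratio | 4 levels | 5 levels | 15 levels |
|---|---|---|---|
| 2.0 | 48% vs 64% | 43–44% vs 65–66% | 22–24% vs 67–69% |
| 2.5 | 73% vs 87% | 68–71% vs 87–88% | 42–43% vs 89–90% |
| 3.0 | 89% vs 96% | 86–87% vs 96–97% | 63% vs 97% |

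Type I error here was about 3–5% for both tests.

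**7. The nominal half.** For a yes/no item, the tie-corrected Mann-Whitney z² equals the Pearson chi-square times (N − 1)/N. At N = 142 this factor is 141/142 = 0.993, so the two tests almost coincide.

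**The case against.** The strongest reply is that this is a slip of word order. The reference to Fisher's exact test sits beside chi-square, where it belongs for sparse counts, and exchanging two names yields a conventional plan. That is plausible and lowers the expected harm. But it is an inference about intent; the rule as published is reversed and still needs correcting.

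The other objections limit the size of the point, and they stand:

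- **Importance.** A reader might infer a threat to the trial's main conclusion. The documents do not support that. The affected outcomes are secondary, sample size rests on FHSQ pain alone, and the primaries are analysed by analysis of covariance.
- **Half the power lost throughout.** A reader might carry the 15-point result over to all three outcomes. At the assumed shift the 4- and 5-level outcomes lose about 14% and 20% in relative terms.
- **The effect size.** The 0.56 SD belongs to FHSQ pain. Using it for satisfaction, stiffness or symptom change is an assumption, and the loss varies with it.
- **The odds ratio.** A reader might infer a second error, because neither test produces the odds ratio named for ordinal data. The plan specifies effect sizes in a separate sentence, and a test and an effect measure need not come from one procedure. Analysis of covariance does not itself output Cohen's d either.

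**Conclusion.** The point holds for the rule as written. The two tests are assigned the wrong way round, and three ordinal secondary outcomes would be compared without regard to category order. The consequence is lost power, not false positives. Chi-square has the lower power in every shift scenario examined, under both models. The size of the loss rests on assumed effect sizes and category distributions that the documents do not give.

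The loss of about half applies to the 15-point scale only, and only if all its categories are kept and it is analysed as ordinal. If it were collapsed or treated as continuous, the largest loss would be that of the 5-point scale, about a fifth to a third across the scenarios at odds ratios of 2.0 to 2.5 and the 0.56 SD shift. The nominal half of the swap does little harm for yes/no items. Severity is moderate to minor.

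**What to change.** Exchange the two test names. Nominal and dichotomous outcomes (the yes/no recommendation, any use of rescue medication, occurrence of adverse events) are compared by chi-square or Fisher's exact test, and ordinal outcomes (stiffness duration, satisfaction, symptom change) by Mann-Whitney. This changes one sentence, needs no new data or procedures, and fully cures the error. It should be recorded before unblinding.

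Proportional-odds regression for the ordinal outcomes is optional. It is one way to obtain the stated odds ratio together with an ordered test, but it brings the proportional-odds assumption, which would then need to be checked.
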